### Aims and research questions

#### Between-person research questions

This observational study aims to (a) describe the health status of the lower back and PA patterns of working people, to (b) examine the relationship between LBP, back health (i.e., behavior-related outcomes) with PA, and to (c) examine theory-based, psychological predictors of workers’ LTPA. At the macro level, we will describe physical activity patterns in workers’ daily lives in terms of intensity, frequency, duration, and type of activity. At the micro level, we will describe posture and movement of the back using self-reported and objective biomechanical measures. We will analyze the back health and physical activity patterns of people in different work contexts. This includes people who work in a sedentary environment (e.g., office work) and people who do manual work as part of their job, such as physiotherapists.

We hypothesize that individuals from different work contexts will differ in their back health and in their levels of LTPA. We also hypothesize that overall higher mean levels of LTPA will be positively associated with workers’ subjective back health, posture and mobility, and negatively associated with pain. Figure 1 shows the set of theory-based, psychological predictors of LTPA intention and LTPA. Based on the Back Health Behavior Model (Fig. 1) we have the following hypotheses. We hypothesize that overall higher mean levels in activity-related cognitions will be positively associated with LTPA intention, with the exception of risk perception and negative outcome expectancies, for which we expect the opposite. We also hypothesize that overall higher mean levels of back-related beliefs, negative affect, and job demands will be negatively associated with LTPA intention. For positive affect, habit, and job resources, we expect positive associations with LTPA intention. We expect a positive association between overall higher mean levels of LTPA motivation and volitional strategies of self-regulation as well as job resources, and the opposite for job demands. Finally, we hypothesize overall higher mean levels of LTPA to be predicted by volitional strategies of self-regulation. We will also explore whether the relationship between back health and job demands and job resources is mediated by LTPA.

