### Power analysis

An a priori power analysis with G*Power [76] was performed for the primary between-subject research questions on the difference between two work contexts for LTPA. At a significance level of 5%, a power of 95%, a medium effect of d = 0.5, and equal sample sizes we would require a sample size of 210 participants. Accounting for a potential dropout of 20%, this increases to a sample size of 252 participants.

A priori power analyses for examining the link between LTPA and behavior-related outcomes (i.e., low back pain) at a significance level of 5% and 95% power, result in different sample sizes, depending on the effect size of the relationship that we expect between the specific behavior-related outcome and LTPA. It ranges from an expected small effect size, resulting in 115 participants, to a medium effect size resulting in 38 participants.

A path analytic approach to test our assumptions on the links between theory-based, psychological variables and LTPA (Fig. 1) necessitates a minimum of 210 participants [77].

Regarding a priori power analyses for multilevel models this study referred to heuristics presented in Arend and Schäfer [78], who had run Monte-Carlo simulations with a minimum of 80% power for different conditions on the smallest necessary sample size. At a significance level of 5%, a minimum of 80% power, a medium intraclass coefficient, and a minimum of *n*_Level−1_ = 14 days of assessment (i.e., number of repeated measurements within persons), small correlations for the primary outcome (LTPA) with a predictor (Level-1/day-level, e.g., intention) [79] would require a minimal Level-2 sample size of *N* = 150 (i.e., number of required individuals). For medium correlations of the outcome with a predictor (Level-2/person-level, e.g., work context), a significance level of 5%, a minimum of 80% power, a medium intraclass coefficient (ICC = 0.50) and a minimum of *n*_Level−1_ = 14 days of assessment, a minimal sample size of *N* = 100 would be required. Considering a potential dropout of 20% for the larger sample size, this estimation increases to *N* = 180.

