#### Hypothesis tests for long-longitudinal phase

Hypotheses on between-group differences will be checked with t-tests. The association between LTPA and behavior-related outcomes with respect to the lower back will be tested with regression models. Path analyses will be used to test our assumptions on the links between theory-based, psychological variables and LTPA (Fig. 1).

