### Strengths, challenges and limitations

One major strength of the *workHealth* study is the multimethod assessment of physical activity including back posture and mobility (i.e., objective assessments and self-reports). Using objective measures overcomes many of the challenges associated with common method variance (e.g., inflated correlations between self-reported predictors and self-reported outcomes) or recall bias. On the other hand, there are several limitations associated with the use of accelerometers including lack of usable data, non-compliance with the wearing protocol and technical failures of the instrument [87]. A major disadvantage of using accelerometers is that it cannot provide information on the type, context and purpose of PA a person has engaged in (e.g., swimming, team sport, etc.). Therefore, the workHealth study combines the PA assessments of the Move4 with self-reports of PA. Similarly, our study combines self-reports of back posture and mobility with objective measurements. For each assessment domain, we will validate the objective assessments with the self-reported data.

A further strength of the *workHealth* study lies in its shift from a pathological view towards a more salutogenic, resource-oriented understanding of LBP [88]. While previous studies have typically been limited to studying modifiable risk factors, including health risk behaviors (e.g., heavy lifting, prolonged sitting) and health-limiting cognitions (e.g., fear of movement, pain catastrophizing), *workHealth* examines these in combination with resources such as health-promoting types of PA and self-efficacy. Furthermore, rather than looking only at the individual, the workHealth study has broadened the view to include the environment in which the individual is located, with a particular focus on the immediate workplace of two unique occupational groups: healthy, sedentary office workers and physiotherapists. Studying LBP in clinically “normal”, healthy individuals comes with methodological challenges, that is, reduced variance in the outcome. In line with the idea that the primary prevention of low back pain is not only aimed at the avoidance or reduction of LBP, but also at the opposite, the promotion of the health of the lower back – the workHealth study, therefore, uses a measure of self-reported health with regard to the lower back in addition to pain ratings.

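### The sample sizes given for the LTPA–low-back link (115 for a small effect, 38 for a medium one) carry labels about one step too favourable, so 115 participants do not give 95% power for a small effect

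*Protocol article*

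**What the plan says.** The Power analysis section of the protocol article makes two calculations at the same significance level and power.

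- **Group comparison of LTPA.** "At a significance level of 5%, a power of 95%, a medium effect of d = 0.5, and equal sample sizes" lead to 210 participants. Then: "Accounting for a potential dropout of 20%, this increases to a sample size of 252 participants".
- **LTPA and low-back outcomes.** The conditions are again "i.e., low back pain) at a significance level of 5% and 95% power". The required number depends on the outcome: "It ranges from an expected small effect size, resulting in 115 participants, to a medium effect size resulting in 38 participants".

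For the second calculation the section gives no effect-size value, no scale (r, f² or other) and no sidedness. The analysis is described under Hypothesis tests for long-longitudinal phase: "The association between LTPA and behavior-related outcomes with respect to the lower back will be tested with regression models". The hypotheses for this link have a direction. Under Between-person research questions, "overall higher mean levels of LTPA will be positively associated with" back health, posture and mobility, and a negative association is expected with pain.

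**The concern.** At one significance level and one power, a smaller effect needs more participants. Here the small effect needs 115, while the medium effect a paragraph earlier needs 210. Different tests and scales can explain some of that gap, so the figures have to be put on a common scale before the labels can be judged.

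The link matters because it is one of the study's three stated aims. A reader who accepts 115 for a small effect will conclude that a cohort of 252 has ample power for weak associations with back pain and back health. The article itself says that studying healthy people "comes with methodological challenges, that is, reduced variance in the outcome", so how well weak associations can be detected is a fair question for this design.

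**Working it through.** **Inputs from the article:** α = 0.05; power 0.95; stated n of 115 and 38; d = 0.5 with equal groups giving 210; 252 recruited; 20% dropout. Analysable participants: 252 × 0.8 = 201.6, about 202, up to 252 with no loss.

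**Assumed, because the article gives no values:** conventional benchmarks r = 0.10, 0.30 and 0.50 for small, medium and large, or f² = 0.02, 0.15 and 0.35. Sidedness is unstated, so both are shown.

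**1. The 210.** A two-sample t-test with d = 0.5 and 95% power needs 210 in total two-sided and 176 one-sided. The 210 is a two-sided figure.

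**2. The 115 and 38.** The Fisher approximation is n = ((z_α + z_β) / atanh r)² + 3, with z_β = 1.645.

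- One-sided, r = 0.30: (3.290 / 0.3095)² + 3 = 115.96. The exact bivariate-normal calculation gives **115**.
- One-sided, r = 0.50: (3.290 / 0.5493)² + 3 = 38.87. The exact calculation gives **38**.

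Both stated figures are matched by one test at two adjacent benchmarks.

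**3. What conventional small and medium effects need (95% power).**

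| Effect | One-sided n | Two-sided n |
|---|---|---|
| Small, r = 0.10 | 1,077 | 1,293 |
| Medium, r = 0.30 | 115 | 138 |
| Large, r = 0.50 | 38 | 46 |
| Small, f² = 0.02, one predictor | 543 | 652 |
| Medium, f² = 0.15, one predictor | 74 | 89 |
| Large, f² = 0.35, one predictor | 33 | 40 |

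Omnibus F tests with one to seven predictors, point-biserial correlations and one-sample d were also tried. Near misses occur singly (119 for f² = 0.15 with three predictors; 40 for f² = 0.35), but no small-and-medium pair gives both stated figures.

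**4. The two calculations on one scale.** With equal groups r = d / √(d² + 4), so d = 0.5 gives 0.5 / √4.25 = 0.243. In the other direction d = 2r / √(1 − r²): r = 0.30 gives 0.63 and r = 0.50 gives 1.15. This comparison does not depend on the sidedness inferred in step 2. The correlation that has 95% power at n = 115 is 0.30 one-sided and 0.33 two-sided, and both exceed 0.243.

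**5. Power for a small effect at the study's size.**

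| Meaning of small | Sidedness | n = 202 | n = 252 |
|---|---|---|---|
| r = 0.10 | two-sided | 29% | 35% |
| r = 0.10 | one-sided | 41% | 48% |
| f² = 0.02 (r = √(0.02/1.02) = 0.14) | two-sided | 52% | 61% |
| f² = 0.02 | one-sided | 64% | 72% |

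At the stated n = 115, power for r = 0.10 is 19% two-sided and 28% one-sided.

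**6. Detectable association at n = 202.** r = tanh((z_α + z_β) / √199), with √199 = 14.107.

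- Two-sided: 95% power at tanh(3.605 / 14.107) = 0.25; 80% power at tanh(2.802 / 14.107) = 0.20.
- One-sided: 95% power at tanh(3.290 / 14.107) = 0.23; 80% power at tanh(2.486 / 14.107) = 0.17.

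**The case against.** The strongest reply is that this calculation sets nothing. The total of 252 comes from the group comparison, and the path analysis separately asks for 210. At 202 evaluable, power for r = 0.30 is above 99%, and for r = 0.20 it is 82% two-sided. All of that stands, and it makes this a correction of the reported figures and not a fault in the design.

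A second reply is that 210 and 38 belong to different tests, and medium need not mean the same on each scale. That is fair as far as the word goes. It does not save the label on 115, because step 4 shows that effect to be larger than d = 0.5 on a common scale under either sidedness.

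Three stronger readings are tempting, and the article does not support them:

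- **That the study has 29% power for a small effect.** This is the least favourable cell in step 5. It needs r = 0.10, a two-sided test and 202 analysable, none of which the article fixes for this link. Only the range can be reported.
- **That the plan switched to one-sided testing without saying so.** The group hypothesis is only that the work contexts differ, which suits the two-sided 210. The hypotheses for this link are directional, which would suit a one-sided calculation. Sidedness is unstated; it is not shown to be inconsistent.
- **That true effects here are small, or that a null result will be misread.** The article concedes reduced outcome variance but does not predict the size of the association, and it adds a back-health rating in response.

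**Conclusion.** The point holds as an error in stated figures. At 5% significance and 95% power, 115 and 38 are correct for a one-sided correlation test at r = 0.30 and r = 0.50. They are not correct for a small and a medium effect on any conventional scale tried. On the r scale a small effect needs roughly nine to eleven times the stated 115 (1,077 / 115 = 9.4; 1,293 / 115 = 11.2). On the f² scale it needs roughly five to six times as many (543 / 115 = 4.7; 652 / 115 = 5.7).

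That 115 and 38 came from one-sided r = 0.30 and 0.50 is an inference from an exact double match, since the article names neither value. The benchmarks for small are also assumed. The conclusion that power for a small effect falls short of 95% does not turn on which benchmark or sidedness is chosen: every combination with 202 to 252 analysable participants lies between about 29% and 72%.

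**What to change.** In the Power analysis section, state the effect-size metric, the numerical value and the sidedness for the LTPA–low-back link. Then do one of the following:

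- Keep 115 and 38 and label them as the numbers for one-sided correlation tests at r = 0.30 and r = 0.50, if that is confirmed as their source.
- Replace them with what the planned size can detect. For example: with about 202 evaluable participants and a two-sided 5% test, power is 95% for r of about 0.25 or more, 80% for r of about 0.20 or more, and about 30% for r = 0.10. If one-sided tests are intended, say so and give those figures instead (95% for r of about 0.23, 80% for about 0.17, 41% for r = 0.10).

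Add that non-significant associations will be interpreted by their confidence intervals.

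The cost is two or three sentences. Recruitment, outcomes and analyses do not change, and 252 stays as it is. The stated power for small effects becomes less favourable.

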### Data analyses

Statistical analyses will be performed separately during data collection for monitoring and at the end of data collection for the main study and for the *N*-of-1 sub-sample. Descriptive statistics will be performed for all variables (Tables 1 and 2) as well as screening for plausibility, evaluation of distributional properties and outliers, and evaluation of missing data.

#### Hypothesis tests for long-longitudinal phase

Hypotheses on between-group differences will be checked with t-tests. The association between LTPA and behavior-related outcomes with respect to the lower back will be tested with regression models. Path analyses will be used to test our assumptions on the links between theory-based, psychological variables and LTPA (Fig. 1).

#### Hypothesis tests for intensive-longitudinal phase

For the IL data with measurement days nested in participants, multilevel models with daily LTPA as outcome will be calculated. Hypothesis tests for the fixed effects will inform us on the daily links between LTPA and its within- and between-person predictors. To test mechanisms from the back health behavior model (Fig. 1), we will specify within-person mediation models and test the indirect effects.

#### Hypothesis tests for intensive-longitudinal phase N-of-1

Separate analyses will be performed for the *N*-of-1 sub-sample, as single case design requires different analysis procedure. Statistical analyses will follow dynamic regression modeling [82, 83]. Structured visual analysis of quantitative variables across the 68 days will be performed, with regards to level, trend, and variability [84]. Qualitative data from the data-prompted interviews in the *N*-of-1 sub-sample will be analyzed with the Framework Method [85] to facilitate a thematic analysis. It will also enable us to integrate qualitative findings with quantitative findings from the EMA part of the *N*-of-1 study in a pragmatic approach.

### Dissemination

The study registration and study protocol are the first publications of the workHealth study. Findings of this study will be published in peer-reviewed international journals and at national and international conferences, separately for the main study and the *N*-of-1 sub-sample. Additional dissemination to the public is planned at public institutional events and via various media.

## Discussion

Individuals can play an active role in the prevention of LBP by reducing health risk behaviors, such as breaking up sedentary time, and engaging in health-promoting PA. This includes both macro-level movements like LTPA, e.g [86], and micro-level movements like adjusting and changing back posture. Currently, there is no consensus as to which physical activity (e.g., domain, intensity, duration) is most beneficial for whom (e.g., healthy individuals in different work contexts) to prevent and to treat LBP. A more detailed understanding of the relationships between LBP and different facets of physical activity and its theory-based psychological predictors is needed to inform future behavioral interventions. The *workHealth* intensive longitudinal observational study addresses this need by integrating evidence, theory and assessment methods from psychology, biomechanics and behavioral medicine.

### Strengths, challenges and limitations

One major strength of the *workHealth* study is the multimethod assessment of physical activity including back posture and mobility (i.e., objective assessments and self-reports). Using objective measures overcomes many of the challenges associated with common method variance (e.g., inflated correlations between self-reported predictors and self-reported outcomes) or recall bias. On the other hand, there are several limitations associated with the use of accelerometers including lack of usable data, non-compliance with the wearing protocol and technical failures of the instrument [87]. A major disadvantage of using accelerometers is that it cannot provide information on the type, context and purpose of PA a person has engaged in (e.g., swimming, team sport, etc.). Therefore, the workHealth study combines the PA assessments of the Move4 with self-reports of PA. Similarly, our study combines self-reports of back posture and mobility with objective measurements. For each assessment domain, we will validate the objective assessments with the self-reported data.

A further strength of the *workHealth* study lies in its shift from a pathological view towards a more salutogenic, resource-oriented understanding of LBP [88]. While previous studies have typically been limited to studying modifiable risk factors, including health risk behaviors (e.g., heavy lifting, prolonged sitting) and health-limiting cognitions (e.g., fear of movement, pain catastrophizing), *workHealth* examines these in combination with resources such as health-promoting types of PA and self-efficacy. Furthermore, rather than looking only at the individual, the workHealth study has broadened the view to include the environment in which the individual is located, with a particular focus on the immediate workplace of two unique occupational groups: healthy, sedentary office workers and physiotherapists. Studying LBP in clinically “normal”, healthy individuals comes with methodological challenges, that is, reduced variance in the outcome. In line with the idea that the primary prevention of low back pain is not only aimed at the avoidance or reduction of LBP, but also at the opposite, the promotion of the health of the lower back – the workHealth study, therefore, uses a measure of self-reported health with regard to the lower back in addition to pain ratings.

The workHealth study is based on theory (Fig. 1) which provides specific testable predictions not only for psychological predictors contributing to LTPA, pain, and back health, but also their temporal alignment in the behavior change process. This provides important information for the development of behavioral interventions. Besides a traditional longitudinal design, the workHealth study employs an intensive longitudinal research design with daily sampling of momentary experiences and behavior in daily life (as opposed to snapshot assessments in the laboratory) which allows for testing of theory-based predictors of PA, LBP and back health within individuals, thereby allowing conclusions to be drawn about within-person dynamics of psychological and behavioral risks and resources for LPB. However, these benefits come with certain risks, such as a high expected drop-out rate or increased participant burden. With the provision of individualized feedback and monetary incentives we anticipate reducing these risks.

In conclusion, despite potential risks and limitations, the knowledge gained from our observational study is intended to advance the understanding of risk factors and resources protecting against the onset of LBP and inspire the future development and evaluation of mhealth applications for behavioral approaches to both LBP prevention and back health promotion.

## Data Availability

No datasets were generated or analysed during the current study.

## Abbreviations

LBP: Low back pain
BMI: Body–Mass–Index
PA: Physical activity
LTPA: Leisure–time physical activity
pamDC: Physical activity–mediated Demand–Control model
HAPA: Health Action Process Approach
PAAM: Physical Activity Adoption and Maintenance
BHBM: Back Health Behavior Model
EMA: Ecological momentary assessment
LL: Long–longitudinal
IL: Intensive–longitudinal
T0: Time 0, baseline
T1: Time 1
T2: Time 2
T3: Time 3
MVPA: Moderate–to–vigorous physical activity
IPAQ: International Physical Activity Questionnaire
MET: Metabolic Equivalent of Task
B-PMM self-report questionnaire: Back posture, movement, and mobility self–report questionnaire
VR-12: Veterans Rand 12–Item Health Survey
HrQoL: Health–related Quality of Life
PHQ-4: Patient Health Questionnaire–4
CPGQ: Chronic Pain Grade Questionnaire
RMDQ: Roland–Morris Disability Questionnaire
PANAS: Positive And Negative Affect Schedule
